## Abstract

**Background:**

Chronic insomnia disorder (CID) is common and often impairs daytime functioning and quality of life. Although cognitive behavioral therapy for insomnia and hypnotic medication are widely used, their clinical use may be limited by accessibility, cost, adherence, and concerns about long-term adverse effects. Acupuncture is commonly used for CID, but conventional acupuncture alone may require a relatively long treatment course. Because sympathetic hyperarousal plays an important role in insomnia, the stellate ganglion (SG) may represent a useful therapeutic target. This trial aims to evaluate the clinical efficacy and potential neurofunctional mechanisms of ultrasound-guided SG acupuncture combined with conventional acupuncture in patients with CID.

**Methods/design:**

This single-center, parallel-group randomized controlled trial will enroll 80 patients with CID, who will be allocated in a 1:1 ratio to a treatment group or a control group. In addition, healthy controls will be recruited for baseline functional near-infrared spectroscopy (fNIRS) comparison only. Before fNIRS acquisition, healthy controls will undergo clinical screening and baseline assessments. The control group will receive conventional acupuncture, whereas the treatment group will receive ultrasound-guided SG acupuncture plus conventional acupuncture. Both groups will receive 12 treatment sessions over 4 weeks. Outcomes will be assessed at baseline, week 4, and week 8. The primary outcomes are the Insomnia Severity Index (ISI) and fNIRS data of brain function. Secondary outcomes include the Pittsburgh Sleep Quality Index (PSQI), Hamilton Anxiety Rating Scale (HAMA), and overall clinical efficacy.

**Discussion:**

This trial will determine whether ultrasound-guided SG acupuncture combined with conventional acupuncture provides additional benefit over conventional acupuncture alone for CID. It will also explore treatment-related changes in brain function by combining clinical scales with fNIRS assessment. The findings may provide more objective evidence for acupuncture-based treatment of CID and help clarify its neurofunctional basis.

**Clinical trial registration:**

https://itmctr.ccebtcm.org.cn/mgt/dashboard, ITMCTR2025000535.

## Introduction

1

Insomnia is a common sleep disorder characterized by difficulty initiating sleep, difficulty maintaining sleep, or early morning awakening, leading to poor sleep quality and impaired daytime functioning (1). When these symptoms occur at least three nights per week for 3 months or longer, the condition is classified as chronic insomnia disorder (CID) (2). According to World Health Organization estimates, CID affects approximately 10–15% of adults worldwide and is associated with substantial adverse outcomes, including cognitive impairment, mood disturbances and reduction in quality of life (3, 4).

Current treatments for insomnia include cognitive behavioral therapy for insomnia (CBT-I), pharmacotherapy, and traditional Chinese medicine approaches (5, 6). Although CBT-I is recommended as first-line therapy, its use is often limited by availability, time burden, and cost, which may reduce uptake and adherence (7–9). Medications can improve sleep in the short term, but long-term use is restricted by concerns about adverse effects, dependence, and cognitive impairment (10).

Acupuncture is widely used for CID because it is relatively low-cost and generally safe, and available evidence suggests that it can improve sleep quality and related symptoms (11–14). However, in view of the multifactorial etiology of CID, conventional acupuncture alone may require a relatively long treatment course, which may in turn affect adherence (15, 16).

Insomnia is frequently associated with sympathetic nervous system (SNS) hyperarousal (17). The stellate ganglion (SG), as a principal node of the SNS, has been implicated in autonomic regulation relevant to sleep (18). Stellate ganglion block (SGB) has been reported to reduce sympathetic outflow, improve sleep quality, shorten sleep latency, and relieve daytime dysfunction (19). However, its wider use is limited by procedure-related adverse effects such as hoarseness, dizziness, and puncture-site hematoma (20). In our clinical practice, SG acupuncture appears to facilitate sleep onset and improve sleep quality, and similar findings have been described in case-based clinical reports (21). Ultrasound-guided SG acupuncture may therefore offer a safer and more practical approach to autonomic modulation while complementing conventional acupuncture.

Most acupuncture trials in CID rely mainly on subjective scales. Functional near-infrared spectroscopy (fNIRS) offers a noninvasive way to assess cortical hemodynamics and functional connectivity (22). Insomnia has been associated with functional alterations in the prefrontal cortex (PFC) (23, 24), and task-evoked PFC activation and resting-state PFC connectivity may provide complementary neurofunctional information (25, 26). Accordingly, fNIRS combined with a verbal fluency task (VFT) has been used to detect reduced PFC activation in CID (25, 27). The VFT is feasible and engages executive-linguistic processes such as lexical retrieval, self-monitoring, and response inhibition (25, 27–29), making it a suitable paradigm for probing prefrontal function in this population.

Building upon these considerations, the present trial is designed to characterize the brain functional features of CID using fNIRS and to determine whether adding ultrasound-guided SG acupuncture to conventional acupuncture provides greater clinical benefit than conventional acupuncture alone. The study is also expected to generate objective neurofunctional evidence for this integrated treatment strategy.

## Methods and analysis

2

### Study design

2.1

The present study is designed as a single-center, parallel-group, randomized controlled trial to be conducted at Tongde Hospital of Zhejiang Province Affiliated to Zhejiang Chinese Medical University, during the period from June 1, 2025 to August 1, 2026. Ethical approval for the study protocol has been granted by the hospital Ethics Committee (No. 2024-098K), and trial registration has been completed in the International Traditional Medicine Clinical Trial Registry (ITMCTR2025000535). The study protocol was developed in accordance with the Standard Protocol Items: Recommendations for Interventional Trials (SPIRIT) guidelines and was guided by the principles of the Consolidated Standards of Reporting Trials (CONSORT) (30) and the Standards for Reporting Interventions in Clinical Trials of Acupuncture (STRICTA) (31).

### Ethics approval

2.2

Written informed consent will be obtained before enrollment. Patients with CID will be randomized to the treatment or control group. A healthy control cohort will undergo baseline clinical screening and fNIRS assessment only, without randomization, acupuncture treatment, or follow-up efficacy assessment. Study-related interventions, assessments, and consultations will be provided free of charge. The study flow is shown in Figure 1, and the assessment schedule is presented in Table 1.

**Figure 1 fig1:**
[figure not shown]
The flowchart of trial procedures.

**Table 1 tab1:** Schedule of enrolment, interventions and outcome assessments.

Timepoint	Baseline		Treatment phase	Follow-up phase
	Week −1	Week 0	Week 1–4	Week 8
Participants				
Eligibility screen	×			
Signed informed consent		×		
Clinical interview		×		
Physical examination		×		
Randomization		×		
Interventions				
treatment group		×	×	
Control group		×	×	
Primary outcomes				
ISI		×	×	×
fNIRS assessment		×	×	×
Secondary outcomes				
PSQI		×	×	×
HAMA		×	×	×
Overall clinical efficacy			×	×
Assessments				
Adverse events		×	×	
Use of sleep medications		×	×	×
Patients’ compliance		×	×	×

ISI, the insomnia severity index; PSQI, Pittsburgh sleep quality index; HAMA, Hamilton anxiety scale. × = Implementation of the corresponding project at the corresponding point in time.

### Sample size calculation

2.3

This trial has two prespecified primary endpoints: change in Insomnia Severity Index (ISI) score and change in task-evoked prefrontal oxygenated hemoglobin (Oxy-Hb) response measured by fNIRS. A Bonferroni-style alpha-allocation strategy will be used to control the family-wise type I error rate, with a two-sided alpha of 0.025 assigned to each primary endpoint. For the ISI endpoint, a 3-point between-group difference was considered clinically meaningful, consistent with the lower bound of minimal clinically important difference estimates for the ISI (32), and supported by a randomized acupuncture trial in primary insomnia (33). Using a pooled SD of 3.8 from a comparable insomnia population (33), the standardized effect size was estimated as Cohen’s *d* = 3.0/3.8 = 0.79. With a two-sided *α* of 0.025, 1:1 allocation, and 80% power, approximately 32 participants per group are required.

For the fNIRS endpoint, a standardized effect size of *d* = 0.80 was assumed for the between-group difference in prefrontal Oxy-Hb change. With alpha = 0.025, 1:1 allocation, and 80% power, approximately 27 participants per group are required. Because the ISI endpoint requires the larger analyzable sample, it is the binding constraint. After allowing for a 20% attrition rate, the required enrollment sample size was calculated as follows:

$$n_{\text{enrolled}}=\frac{n_{\text{required}}}{1-\text{attrition rate}}=\frac{32}{1-0.20}=40$$

Thus, 40 participants per group, for a total of 80 participants, will be randomized.

Sensitivity analysis showed that, with 32 analyzable participants per group, the study would retain approximately 80.4% power for ISI and 81.4% power for fNIRS Oxy-Hb at alpha = 0.025. If the true fNIRS effect decreases to *d* = 0.75, power would decrease to approximately 75.7%, indicating that the fNIRS endpoint is more sensitive to effect-size assumptions. Strict fNIRS acquisition, preprocessing, and quality-control procedures will therefore be implemented. Previous fNIRS acupuncture studies have generally included 12–20 participants (34–36). On this basis, at least 20 participants per group will be included in the fNIRS analysis. After allowing for an anticipated dropout rate of 20%, 24 healthy controls per group will be planned for fNIRS assessment.

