Data Preprocessing: First, the raw light intensity data will be converted to optical density (OD). Second, motion artifacts will be identified and corrected using spline interpolation. Third, a band-pass filter (0.01–0.1 Hz) will be applied to the OD data to reduce physiological noise (e.g., heartbeat, respiration) and low-frequency signal drift. Finally, the filtered OD data will be converted to relative concentration changes in oxy-Hb, deoxyhemoglobin (deoxy-Hb), and total hemoglobin (tHb) using the modified Beer–Lambert law. The differential pathlength factor (DPF) will be set to 6.0 for both 690 nm and 830 nm wavelengths.

Quality Control: Channel signal quality will be evaluated using the coefficient of variation (CV), which will be calculated based on the raw light intensity during the initial resting period. Channels with a CV > 15% will be considered to have excessive noise and will be excluded from further analyses (44). Participants with more than 20% of their channels categorized as low-quality will be entirely removed from the group-level fNIRS analysis.

Feature Extraction: In accordance with standard practices, oxy-Hb will serve as the primary indicator of cortical activation due to its higher sensitivity to task-related changes (45). To quantify task-evoked activation during the VFT, a GLM will be applied at the individual level. The design matrix will include the task conditions convoluted with a canonical hemodynamic response function (cHRF). Task-related regression coefficients (*β* values) will be extracted to represent the activation strength for each channel. For region-of-interest (ROI) analyses, the extracted *β* values from channels located within the bilateral dorsolateral prefrontal cortex (DLPFC) and medial prefrontal cortex (mPFC) will be averaged.

Longitudinal comparisons of ROI metrics (baseline, week 4, and week 8) will be conducted using independent-samples *t*-tests or Mann–Whitney *U* tests for comparisons between groups at each time point, with FDR correction applied to multiple fNIRS comparisons.

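### The fNIRS primary endpoint needs 31 analyzable participants per group on the stated inputs, not 27, so the planned 32 leave a margin of one per arm rather than five

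*Protocol article*

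**What the plan says.** Section 2.3 (Sample size calculation) names two primary endpoints, ISI change and task-evoked prefrontal Oxy-Hb change, "with a two-sided alpha of 0.025 assigned to each primary endpoint". For ISI it takes d = 3.0/3.8 = 0.79 and requires 32 per group. For fNIRS an effect size of "0.80 was assumed for the between-group difference in prefrontal Oxy-Hb change", followed by: "With alpha = 0.025, 1:1 allocation, and 80% power, approximately 27 participants per group are required". It then concludes: "Because the ISI endpoint requires the larger analyzable sample, it is the binding constraint". Attrition of 20% takes 32 to 40 randomized per group. The next paragraph reports that 32 analyzable per group give 80.4% power for ISI and 81.4% for fNIRS, or 75.7% for fNIRS if d is 0.75.

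The same paragraph cites earlier fNIRS acupuncture studies of 12–20 participants and continues: "On this basis, at least 20 participants per group will be included in the fNIRS analysis". After a 20% dropout allowance, "24 healthy controls per group will be planned for fNIRS assessment".

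Section 2.11 (Data analysis, Quality Control) adds a loss that section 2.3 does not mention: "Participants with more than 20% of their channels categorized as low-quality will be entirely removed from the group-level fNIRS analysis".

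**The concern.** ISI at d = 0.79 is said to need 32 per group, while fNIRS at d = 0.80, with the same alpha, power and allocation, is said to need 27. A change of 0.01 in d cannot save five participants per arm. Nor can 27 per group give 80% power when 32 give only 81.4%.

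The figure matters because of the comfort it suggests. A reader who sees 27 against 32 will think that five fNIRS data sets per arm can be lost before power drops below 80%. This endpoint is the one exposed to an extra loss, since section 2.11 removes whole participants for poor channels. The floor of 20 per group and the healthy-control number stand in the same paragraph as the power figures, and both need attention.

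**Working it through.** **Inputs** (protocol article, section 2.3): fNIRS d = 0.80; ISI d = 0.79; two-sided alpha 0.025 per endpoint; power 80%; 1:1 allocation; attrition 20%. The rate of quality-control removal is not given anywhere, so it is an assumption below.

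**1. The section's other figures reproduce.** With the two-sample t-test (noncentral t) at two-sided alpha 0.025:
- ISI, d = 0.79: n = 31.75, so 32 per group (stated 32).
- ISI at 32 per group: 80.35% (stated 80.4%).
- fNIRS at 32 per group, d = 0.80: 81.42% (stated 81.4%).
- fNIRS at 32 per group, d = 0.75: 75.73% (stated 75.7%).

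This fixes the method the authors used.

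**2. The 27 does not reproduce.**
- Normal approximation: n = 2(z for 0.9875 + z for 0.80)² / d² = 2(2.241 + 0.842)² / 0.64 = 2 × 9.505 / 0.64 = 29.7, so 30 per group.
- t-test: n = 30.99, so 31 per group.
- Cross-check from the section's own ISI figure: required n scales with 1/d², so 32 × (0.79/0.80)² = 31.2.
- At 27 per group and d = 0.80, t-test power is 73.5% (75.7% by the normal approximation). To reach 80% with 27, d would have to be 0.86.
- Two-sided alpha 0.05, without the Bonferroni split, gives 25.5, so 26. That is close to 27 but does not match it, so the origin of 27 stays unknown.

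**3. Effect on enrolment.** 31 / (1 − 0.20) = 38.75, so 39 per group. The planned 40 cover this, and ISI at 32 still needs one more than fNIRS at 31.

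**4. The real margin.** The fNIRS endpoint can lose 32 − 31 = 1 participant per arm, or 1/32 = 3.1%, before power drops below 80%. If quality-control removals come on top of the 20% attrition (rates assumed):

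| Assumed loss | Analyzable per group | Power, d = 0.80 |
|---|---|---|
| 0% | 32 | 81.4% |
| 3% | 32 × 0.97 = 31.0 | 80.1% |
| 5% | 32 × 0.95 = 30.4 | 79.1% |
| 10% | 32 × 0.90 = 28.8 | 76.6% |
| 20% | 32 × 0.80 = 25.6 | 70.8% |

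**5. The floor of 20.** At 20 per group and d = 0.80, t-test power is 58.1%. This bears on the primary endpoint only if the floor applies to the randomized arms.

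**6. Healthy controls.** The section's own formula gives 20 / (1 − 0.20) = 25. The stated 24 is 20 × 1.2, and 24 × 0.80 = 19.2, below the stated minimum of 20. Sections 2.2 and 2.5 describe a single healthy cohort, so a number per group does not fit it.

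**The case against.** The strongest reply is that nothing is sized on 27. Enrolment rests on ISI, the 81.4% at 32 per group is correct, and with 31 in place of 27 the trial still randomizes 40 per group. All of that stands. A reader might infer that the fNIRS endpoint lacks its 80% power as planned, or that the statement making ISI the binding endpoint is false. The document supports neither: planned power at 32 analyzable is above 80%, and 32 still exceeds 31.

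The second reply is that any shortfall from quality control depends on a rate the protocol does not give. The section speaks of analyzable participants, so the 20% may already cover unusable recordings, and section 2.8.3 plans coupling and signal checks before recording. Section 2.11 also plans multiple imputation under intention to treat, which would not simply drop a participant for one failed session. This stands too. A larger loss could be built by requiring both the baseline and the week 4 session to pass independently, but the document states no such requirement. What remains is an unstated point on a margin of one per arm.

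Third, the floor of 20 is followed at once by the healthy-control number and looks like its base. It is also a minimum, and section 2.8.3 schedules fNIRS for all patients. A reader might take 58% as the planned power of the primary endpoint; the text does not establish that. It does leave the floor unattached to any comparison, directly after the power figures for that endpoint.

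Finally, the Discussion warns that smaller neurofunctional effects may be underpowered. That does not correct 27, which is wrong at the assumed d of 0.80.

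**Conclusion.** The stated fNIRS requirement of 27 per group is wrong as written. On the section's own inputs it is 31 (30 by the normal approximation), 27 gives 73.5% power, and the figure contradicts the 81.4% at 32. This rests on no outside assumption.

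The consequence is limited. The 40 randomized per group, the 81.4% at 32 analyzable and the role of ISI as binding endpoint are all unaffected. The true fNIRS margin is one participant per arm, so power falls below 80% if quality-control removals exceed about 3% beyond the 20% attrition. Whether that will happen cannot be judged from the document; the figures for 5% and 10% loss are illustrations. The floor of 20 is ambiguous rather than a demonstrated loss of power. The healthy-control number is a small separate slip against the section's own formula.

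**What to change.** In section 2.3:
- Replace 27 with 31 per group.
- Keep the statement that ISI is the binding endpoint, and add that it exceeds fNIRS by only one participant per arm (32 against 31).
- State whether the 20% attrition includes fNIRS quality-control exclusions under section 2.11. If it does not, report fNIRS power over a range of quality-control loss labelled as assumed, for example 79.1% at 5% and 76.6% at 10%.
- Say that the minimum of 20 per group governs only the comparison of patients with healthy controls.
- Plan 25 healthy controls as one cohort, and drop the wording per group.

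The cost is a text correction and one more healthy control. If quality-control loss lies outside the 20%, the reported fNIRS power becomes somewhat less favourable. No additional randomized patients are needed.

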### Data analysis

2.11

All statistical analyses will be performed by an independent statistician using SPSS version 29.0 (IBM Corp., Armonk, NY, USA) and R software (version 4.3.x). The primary analysis will follow the intention-to-treat principle, including all randomized participants; per-protocol analysis will be used as sensitivity analysis. Continuous variables will be summarized as mean ± SD or median (IQR), and categorical variables as counts and percentages. Baseline characteristics will be summarized descriptively, with standardized mean differences used to assess group balance. No formal baseline hypothesis testing will be performed. Baseline fNIRS comparisons between patients with CID and healthy controls will use ANCOVA controlling for age, sex, BMI, caffeine/alcohol intake, and recording time.

Longitudinal continuous outcomes will be analyzed using linear mixed-effects models with fixed effects for group, time, and group-by-time interaction, and a random intercept for each participant. The main treatment effect will be the between-group difference in change from baseline to week 4; week 8 will be analyzed as follow-up. An unstructured covariance matrix will be attempted first; if convergence fails, AR(1) or compound symmetry structures will be considered based on model fit. Missing data will be handled under the missing-at-random assumption using multiple imputation by chained equations with 20 datasets. The imputation model will include treatment group, time, baseline and available follow-up values, and relevant variables such as age, sex, ISI, PSQI, and HAMA. Results will be pooled using Rubin’s rules.

This is a superiority trial. For ISI, the null hypothesis is no between-group difference in change from baseline to week 4; the alternative is greater improvement in the treatment group. A 3-point ISI difference will be used for sample-size estimation and clinical interpretation but not as a noninferiority or superiority margin. Because there are two primary endpoints, a two-sided Bonferroni-adjusted alpha of 0.025 will be used for each. Secondary outcomes and exploratory fNIRS endpoints will be adjusted using the false discovery rate method where appropriate.

Raw fNIRS data will be processed using NirMaster software (Znion, Wuhan, China). To ensure transparency and reproducibility, the data analysis pipeline will follow standard fNIRS processing procedures, structured into preprocessing, quality control, and feature extraction.

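### The fNIRS co-primary sample size of 27 per group does not follow from its stated inputs: they require 31, and 27 gives 73.5% power, not 80%

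*Protocol article*

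**What the plan says.** Section 2.3 (Sample size calculation) names two primary endpoints, change in ISI and change in task-evoked prefrontal Oxy-Hb, and splits alpha between them, "with a two-sided alpha of 0.025 assigned to each primary endpoint". Section 2.11 (Data analysis) repeats this: "a two-sided Bonferroni-adjusted alpha of 0.025 will be used for each".

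- **ISI.** With d = 3.0/3.8 = 0.79 and 80% power, "approximately 32 participants per group are required".
- **fNIRS.** A standardized effect of "0.80 was assumed for the between-group difference in prefrontal Oxy-Hb change", and then: "With alpha = 0.025, 1:1 allocation, and 80% power, approximately 27 participants per group are required".

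The section concludes: "Because the ISI endpoint requires the larger analyzable sample, it is the binding constraint". It inflates 32 for 20% attrition to reach 40 per group, 80 in total. A sensitivity statement follows: with 32 analyzable per group, "the study would retain approximately 80.4% power for ISI and 81.4% power for fNIRS Oxy-Hb", and fNIRS power falls to about 75.7% if d is 0.75.

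**The concern.** The two endpoints share the same alpha, power and allocation, and their effect sizes are almost equal (0.79 and 0.80). Yet one is said to need 32 per group and the other 27. A change of 0.01 in d cannot remove five participants per group. The fNIRS figure also conflicts with the section's own 81.4% power at 32.

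This is the stated requirement of a co-primary endpoint, and the argument that ISI drives the sample size uses it. Taken at face value, fNIRS could lose five of the 32 expected analyzable participants per group and keep 80% power. The fNIRS analysis has a loss route that ISI does not: under Quality Control in section 2.11, a participant with more than 20% low-quality channels is dropped from the group-level fNIRS analysis. A reader judging whether the trial can absorb such losses would be misled.

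**Working it through.** **Inputs** (section 2.3; alpha also in section 2.11): two-sided alpha 0.025, 1:1 allocation, 80% power, d = 0.80 for fNIRS and d = 3.0/3.8 = 0.79 for ISI.

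**Method.** Two-sample t-test with n per group, df = 2n − 2, noncentrality δ = d·√(n/2) and critical value c = t(0.9875; df). Power = P(T > c) + P(T < −c), with T noncentral t.

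**Step 1: reproduce the section's other figures.**

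| Endpoint | d | n per group | Stated | Recomputed |
|---|---|---|---|---|
| ISI | 0.79 | 32 | 80.4% | 80.4% (80.3% with 3/3.8 unrounded) |
| fNIRS | 0.80 | 32 | 81.4% | 81.4% |
| fNIRS | 0.75 | 32 | 75.7% | 75.7% |

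For ISI, 31 per group gives 78.9%, so 32 is the correct requirement. The exact t-test at two-sided 0.025 is therefore the method behind these numbers.

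**Step 2: apply the same method to the fNIRS requirement (d = 0.80).**

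| n per group | Power |
|---|---|
| 27 | 73.5% |
| 29 | 76.9% |
| 30 | 78.5% |
| 31 | 80.0% |
| 32 | 81.4% |

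The smallest n reaching 80% is 31. The stated 27 is 4/31 = 13% too low. To have 80% power at 27 per group, d would have to be 0.86.

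**Step 3: normal approximation, as the most lenient reading.** n = 2(z₀.₉₈₇₅ + z₀.₈₀)²/d² = 2(2.2414 + 0.8416)²/0.64 = 29.7, so 30 per group. Power at 27 is then 75.7%. This does not give 27 either.

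**Step 4: other readings.** At two-sided 0.05 (or one-sided 0.025) the exact t-test needs 26 per group, the normal approximation needs 25, and 27 per group gives 82.2% (exact t). That is close to the stated figure but is not the stated alpha.

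**Step 5: effect on enrollment and margin.**
- 31/(1 − 0.20) = 38.75, so 39 per group; the planned 40 covers it.
- Margin below 32 analyzable: 32 − 31 = 1 per group (1/32 = 3.1%), against an apparent 32 − 27 = 5 per group (5/32 = 15.6%). By the normal approximation it is 2.

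**The case against.** The strongest reply is that nothing in the design depends on the 27. Enrollment is computed from the ISI figure of 32, and 40 per group covers a corrected fNIRS requirement. Power at the planned 32 is given correctly as 81.4%, so a careful reader can see that the margin is thin. The section itself says fNIRS is the more sensitive endpoint, and the Discussion concedes that smaller neurofunctional effects may be underpowered. ISI also remains the larger requirement after correction (32 against 31), so the binding-constraint sentence is literally true. The article claims no reserve of five and gives no expected rate of fNIRS exclusions, and its 20% could be meant to include them.

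Most of this stands, and it limits the consequence. It does not rescue the figure: a gap of three or four is more than the word approximately can cover, and the caveat about smaller effects does not address a shortfall at the assumed d = 0.80. The objection is also right that the cause is unknown. An unadjusted alpha of 0.05 comes near 27 but gives 26, so it is a possible explanation and no more.

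**Conclusion.** The error is confirmed. Under the stated inputs the fNIRS endpoint needs 31 per group (30 if the normal approximation is used and named), not 27, and 27 gives 73.5% power (75.7% by the approximation). The exact figures are preferred because the same method reproduces the other power values in section 2.3.

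The total of 80 stands. What is wrong is a stated requirement for a primary endpoint and the impression it gives of room to lose fNIRS data. The consequence for that room rests on an assumption: that signal-quality exclusions come on top of the 20% attrition, which the article does not settle. If they do, losing two of 32 per group (6%) leaves 30 and 78.5% power, and fNIRS rather than ISI limits the trial. If the 20% already includes them, 32 analyzable per group gives the stated 81.4%.

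**What to change.** In section 2.3:

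1. Replace 27 by 31 per group (or by 30, naming the normal approximation).
2. State that fNIRS keeps 80% power only with at least 31 analyzable participants per group, one fewer than the 32 expected after attrition.
3. Qualify the binding-constraint sentence: ISI sets the sample size by one participant per group, provided that almost no one beyond the 20% attrition is unusable for fNIRS. Say whether the 20% includes signal-quality exclusions.
4. Add fNIRS power for plausible losses, labelled as illustrative: 76.9% at 29 and 73.5% at 27 analyzable per group.

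The cost is a few sentences and a slightly less favourable stated figure. Enrollment, alpha allocation and analysis do not change.
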